### Reliability of diagnoses and PANSS scores

The two field researchers attended a five day, WHO-certified training course in using the SCAN and a local two day training course in administering the PANSS to the training standard of interrater concordance between field researchers and trainers. The interrater reliability method used was descriptive, according to agreement within one rating point on the positive and negative subscales and within three rating points on the general psychopathology subscale. To achieve interrater reliability on the total PANSS scores, agreement between the field researcher and trainer had to be within the 80% range. Throughout the study, we will conduct interrater reliability maintenance checks of the SCAN and PANSS, with live interviews, to avoid drift in scoring across time.

### Sample size

The primary outcome of the study is the difference between the randomised groups on the number of young people with FEP referred to EIS during the study period, analysed on the basis of intention to treat. As the GPs, rather than their patients, are the subjects of the study, the statistical analysis and thus power calculation accounts for this.

Assuming the standard critical value for α (2 sided p = 0.05), and further that, on average, two referrals will be made in control practices in the study period, and that the variance for between practice variability is one, the study has 80% power (1-β) to detect a mean difference of 1.2 referrals between intervention and control practices, and 90% power (1-β) to detect a mean difference of 1.4 referrals.

As this study is the first randomised trial of an educational intervention in primary care which aims to influence detection and referral practice of GPs, we have no data upon which to base power calculations for the secondary outcome measures which may be considered exploratory (and which will provide relevant data for any future studies).

### Blinding

The participants and field researchers assessing patient outcomes were blinded to the identity of practices that participated in the educational intervention. Statistical analysis follows a pre-specified analysis plan.

### Statistical analysis plan

The effect of the intervention on the primary outcome will be estimated using a non linear mixed model, where the number of referrals per practice will be modelled using Poisson error, and overdispersion (extra Poissonian variability) will be accounted for by defining the practice as a random effect [46]. Analyses will be conducted using Proc Nlmixed in the SAS statistical programme, version 9 [47].

Secondary outcomes will be analysed using a mixed modelling strategy, accounting for between practice variability by defining practices as random effects. As the subject of the experiment is the practice rather than the patient, the denominator degrees of freedom for the analysis will be derived from that stratum.

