### Study aims

The primary aim of the Redirect trial is to estimate whether an educational intervention targeted at GPs increases the GP referral rate of young people with FEP to EIS.

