### Design and randomisation of general practices

The study is a stratified-cluster randomised controlled trial design [32,33]. The cluster design at practice level reduces the risk that the educational intervention delivered to GPs will be contaminated by interaction between GPs within a single practice. Practices were randomly allocated after stratifying by list size (more or less than 3,500 patients) and PCT (HoB or not). These strata were used to ensure balance on the number of practices where no referrals of FEP might occur and to account for the differential prevalence of FEP across the study area. Practices were randomly allocated to either the intervention (39 practices) or control group (39 practices) by NF, who was blind to practice identity, using computer generated random numbers. Figure 1 shows the trial profile summarising practice recruitment and retention.

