### Characteristics of participating practices

The practice characteristics of participating and non-participating practices are summarised in Table 3 and suggest that the participating practices are representative and that the randomisation, after stratification by practice list size and PCT, has been effective.

**Table 3 T3:** Practice characteristics at baseline

	Intervention Practices (*n *= 39)	Control Practices (*n *= 39)	Practices Declined (*n *= 11)
Mean practice list size (range)	4200 (924–10377)	4083 (1465–9927)	4149 (1300–9598)
Single-handed practices	17 (44%)	17 (44%)	6 (55%)
Mean No. of senior partners per practice (range)	2.35 (1–8)	2.03 (1–7)	1.81 (1–4)
Total number of GPs	80	67	20

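### The primary model as described names no term for practice list size or the randomisation strata, and so forgoes precision that adjustment would give at almost no cost

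*Protocol article*

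**What the plan says.** The Statistical analysis plan section of the protocol article describes the primary model: "the number of referrals per practice will be modelled using Poisson error", with extra-Poisson variability handled by a random effect for practice, fitted in SAS Proc Nlmixed. It mentions no offset, list-size covariate or stratum term.

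The Design and randomisation section says: "Practices were randomly allocated after stratifying by list size (more or less than 3,500 patients) and PCT (HoB or not". It gives the reasons: to balance the number of practices that might make no referral at all, and to allow for prevalence that differs across the area. Both reasons tie the strata to the expected number of referrals.

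Table 3 gives mean list size and range as "4200 (924–10377") in the intervention arm and 4083 (1465 to 9927) in the control arm.

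The Sample size section assumes that "on average, two referrals will be made in control practices in the study period" and that "the variance for between practice variability is one". It claims "80% power (1-β) to detect a mean difference of 1.2 referrals between intervention and control practices", and 90% power for a difference of 1.4. It does not say what the variance of one is made of.

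The Blinding section refers to a pre-specified analysis plan, which is not shown.

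**The concern.** The design treats list size and PCT as predictors of the outcome; the described model does not use them. Variation that list size and PCT could explain then falls into the practice random effect, where it counts as noise and widens the standard error of the intervention effect. With 39 practices per arm and about two referrals per practice, the trial has little information to spare.

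If adjustment is not fixed in advance, there is also a choice between adjusted and unadjusted results once the data are seen. At stake are the precision of the primary estimate and the clarity of the primary specification, not the validity of the test.

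**Working it through.** **Inputs.** From the Sample size section: two-sided alpha 0.05, control mean 2, between-practice variance 1, differences d = 1.2 and 1.4. From the Design section: 39 practices per arm. From Table 3: the list-size ranges.

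**1. Reproducing the stated power.** Take the variance per practice as Poisson mean plus 1:

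power = Φ( d / √[((2 + 1) + (2 + d + 1)) / 39] − 1.96 )

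- d = 1.2: √(7.2/39) = 0.430; 1.2/0.430 = 2.79; power 79.8%.
- d = 1.4: √(7.4/39) = 0.436; 1.4/0.436 = 3.21; power 89.5%.

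These match the stated 80% and 90%. The between-practice variance of one is therefore already counted as noise in the stated power.

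**2. If the variance of one includes list size.** Let list size explain a share f of it, and replace each 1 under the root by (1 − f):

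| f | d = 1.2 | d = 1.4 |
|---|---|---|
| 0 | 79.8% | 89.5% |
| 0.25 | 82.5% | 91.4% |
| 0.5 | 85.3% | 93.3% |
| 0.75 | 88.1% | 94.9% |
| 1 | 90.8% | 96.4% |

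The gain from adjustment is 0 to 11.0 points (d = 1.2) or 0 to 6.9 points (d = 1.4). Log-scale versions of the formula give larger ceilings for d = 1.2 (72.6% to 90.3%, or 77.8% to 90.3%, depending on how the variance is scaled), but they do not reproduce the stated power.

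**3. How much variance list size could carry.** The overall spread is 10377/924 = 11.2-fold; within the control arm it is 9927/1465 = 6.8-fold. The expected range of 39 standard normal values is 4.30 SD. Assuming log-normal list sizes, the log SD is ln(11.2)/4.30 = 0.56 and ln(6.8)/4.30 = 0.445, so the CV is about 0.61 and 0.47. If referrals are proportional to list size, the variance at a mean of 2 is 4 × CV², or 0.88 to 1.49, against a planned one. If referrals rise only with the square root of list size (slope 0.5 on the log scale), a log SD of 0.52 gives CV² of 0.07 and a variance of 4 × 0.07 = 0.28.

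**4. If the variance of one excludes list size.** Add (mean × CV)² to each arm's variance, again assuming proportionality:

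| Assumed CV | d = 1.2 | d = 1.4 |
|---|---|---|
| 0.4 | 68.2% | 79.4% |
| 0.5 | 62.7% | 74.0% |
| 0.6 | 56.9% | 67.9% |

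Only on this reading does power fall below the stated figures because of list size.

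**5. Simulation of a Poisson log-normal mixed model.** 3,000 trials per scenario, 2 versus 3.2 referrals (ratio 1.6), allocation stratified at 3,500, assumed log list-size SD 0.52 (CV² = e^(0.52²) − 1 = 0.31):

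| Scenario | Unadjusted | Size stratum | Log list size | Gain, log list size |
|---|---|---|---|---|
| Proportional, no other heterogeneity | 72.9% | 81.5% | 89.6% | 16.7 |
| Slope 0.5, total CV² 0.25 | 74.4% | 77.0% | 78.4% | 4.0 |
| Proportional, plus residual CV² 0.25 | 56.5% | 64.5% | 71.3% | 14.8 |

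The Monte Carlo standard error is at most √(0.25/3000) = 0.9 points. The first scenario implies a variance of 4 × 0.31 = 1.24 at the control mean, somewhat above the planned one. PCT was not simulated, nor were the size stratum and log list size fitted together.

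**6. Validity.** With no intervention effect, in the third scenario's setting, rejection was 3.8% unadjusted, 5.5% with the size stratum and 5.6% with log list size. The unadjusted test is slightly conservative. Mean list sizes differ by (4200 − 4083)/4083 = 2.9%.

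**The case against.** The strongest reply is that silence is not exclusion. The section names no link function and lists no fixed effects; even the intervention term is only implied. The article condenses a pre-specified plan, and covariates are the kind of detail left to such a plan. This stands in part: nobody can say from the article that the analysis will be unadjusted. But the section is specific about where the extra-Poisson variability goes, and the article's own design gives the reason to treat it otherwise.

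Three stronger readings are tempting, and the documents support none of them.

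- **A fixed loss.** A reader might infer that some 10 to 15 points of power are lost. The article gives neither the share of the variance due to list size nor the strength of the dependence, and its stated power already carries a between-practice variance of one. If that variance includes list size, nothing is lost against 80% or 90%; a gain is forgone.
- **Bias or invalidity.** The random effect absorbs the spread, stratification balances it, and the reported mean list sizes are close.
- **A wrong estimand.** The aim speaks of whether the intervention "increases the GP referral rate of young people with FEP to EIS", while the model uses counts. But the Outcomes and Sample size sections define the outcome as a number of referrals, measured at practice level over a common two-year window. A count per practice is then a rate per practice, and nothing defines the rate per registered patient.

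**Conclusion.** The point holds as an efficiency improvement, not as an error that must be corrected. The described model omits variables that the design itself treats as prognostic, and following it as written would leave explainable variation in the random effect.

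The gain from adjustment is a range that depends on assumptions. It is 0 to 11 points for a difference of 1.2 and 0 to 7 points for 1.4 on the formula that matches the stated power, and about 4 to 17 points in the simulations. The main drivers are how steeply referrals rise with list size and what else varies between practices. The list-size spread is itself inferred from sample extremes under an assumed distribution.

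A shortfall against the stated power (to about 57% to 68% for a difference of 1.2, with an assumed CV of 0.6 to 0.4 and proportionality) arises only if the variance of one was meant to exclude list size. The article leaves that open.

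**What to change.** Before outcome analysis, specify the primary Poisson mixed model with the practice random effect, fixed effects for the list-size stratum and the PCT stratum, and log list size as a covariate. Estimating the slope avoids forcing proportionality, as an offset would. Report the ratio with its 95% CI, and keep the unadjusted count model as a sensitivity analysis. In the Sample size text, say whether the variance of one includes list-size variation.

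If the separate analysis plan already contains these terms, only the published description needs to change to match it.

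The cost is three extra coefficients in the Nlmixed code. List size and stratum were needed for randomisation and are held for every practice, so no new data and no operational change are required.

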### Practices recruited

A total of 78 practices out of 89 eligible practices were recruited between July 2003 and October 2003 (Figure 1). The 11 practices that declined to participate cited staffing problems and/or time pressures as the main reasons for non-participation.

### Characteristics of participating practices

The practice characteristics of participating and non-participating practices are summarised in Table 3 and suggest that the participating practices are representative and that the randomisation, after stratification by practice list size and PCT, has been effective.

**Table 3 T3:** Practice characteristics at baseline

	Intervention Practices (*n *= 39)	Control Practices (*n *= 39)	Practices Declined (*n *= 11)
Mean practice list size (range)	4200 (924–10377)	4083 (1465–9927)	4149 (1300–9598)
Single-handed practices	17 (44%)	17 (44%)	6 (55%)
Mean No. of senior partners per practice (range)	2.35 (1–8)	2.03 (1–7)	1.81 (1–4)
Total number of GPs	80	67	20

### Attendance at education intervention and GP feedback

All 39 practices (100%) were represented by one or more GPs at the initial video-based education sessions. Feedback forms on the video were completed by 53 of the 62 GPs (85% response rate). The majority of GPs who participated in the video training agreed or strongly agreed that the video helped them to identify key information to assist their consultations (89%), highlighted useful questions to ask patients (81%), and would improve their confidence in their ability to detect FEP (66%).

### Attendance at refresher education and GP feedback

Thirty-five GPs, representing 26 practices (66.7%), attended the refresher education session and one practice (eight GPs) was visited by the first author. Feedback was obtained from 31 GPs (response rate 89%). Training was perceived as effective in raising awareness of FEP (87%) and the referral process to early intervention services (84%), and GPs reported that the training was relevant (84%), enjoyable (87%), and informative (84%).

## Discussion

The Redirect trial has been designed to evaluate the effectiveness of an educational intervention targeted at GPs on the detection of young people with FEP on referrals to EIS. The educational intervention was designed to be feasible to implement in a busy primary care setting and acceptable to GPs. Recruitment of practices into the trial itself was helped by ensuring that GP time and involvement in the study was kept to a minimum, in recognition of the workload pressures that many UK GPs currently face, particularly with the implementation of the new GMS GP contract [20]. All patients are therefore being recruited from the EIS.

The full support and co-operation of the PCTs, in particular the Heart of Birmingham PCT who enabled the study team to use the bi-monthly PCT protected learning time session to deliver the video based education, was also key to the success of implementing the intervention.

### Strengths

The practice recruitment and retention rates were excellent, ensuring the generalisability of the study findings. Seventy-eight out of 89 eligible practices were recruited, a response rate of 87.6%. To date, there has been a low drop-out rate (one practice). We used a stratified-cluster design [32] to ensure a balanced randomisation for social deprivation, which we believe may affect patient-level outcomes. We are recruiting patients directly from specialist secondary care services, and patient outcomes are based on structured interviews and self-report. The GPs positively evaluated key elements of the initial education video and refresher education, and the good attendance at both these events suggests that this educational intervention is feasible and acceptable in a primary care setting.

### Limitations

It was not possible to accurately assess whether the GPs actually used the written materials that accompanied the video (booklet and laminated 'tip' sheet) during consultations. GPs may have disseminated their copy of the written materials to control group GPs in their area and the extent of contamination between intervention and control group practices is therefore unknown.

## Conclusion

FEP is a devastating diagnosis for the individual and their family. GPs appear to be key players in the referral pathway into EIS and therefore play an important role in the early identification of FEP and potentially in reducing DUP. The Redirect trial, which will report in 2006, will provide robust information about the efficacy of an evidence-based complex educational intervention targeted at GPs on referral rates of young people with FEP to EIS.
